#### **6.1.5 Identifying SUSARs**

The assessment of expectedness for SAEs and regulatory reporting will be undertaken by the CRUK CTU Glasgow Pharmacovigilance office and CI. Expectedness assessments are based on the section of the trial Reference Safety Information (RSI) that has regulatory approval within the DSUR reporting period (and keeping the RSI the same throughout each reporting period) at the time the SAE is received.

When deciding if an event is unexpected consideration will be made by the CI as to whether the event adds significant information of the specificity, increase of occurrence or severity of a known, serious adverse reaction that is already recognised and documented in the RSI. Please note that for unlicensed IMPs any SAR that is fatal or life-threatening will automatically be reported as a SUSAR whether recorded in the RSI as an AE with fatal outcome, or not.

#### **6.1.6 Reporting of a SUSAR**

CRUK CTU on behalf of the (Co) Sponsor is responsible for the expedited reporting of all SUSARs to the required Regulatory Authorities, Research Ethics Committee, PIs at trial sites and the trial Sponsor(s) as well as pharmaceutical company (if applicable). The reporting of SUSARs starts with the authorisation of the clinical trial by any Regulatory Authority in the EU. It ends with the completion of the trial for all patients recruited (from the EU).

- Fatal or life threatening SUSARs will be reported within 7 days of the CRUK CTU receiving the first notification of the unexpected event. Any additional information will be reported within eight days of sending the initial report
- All other SUSARs will be reported within 15 days of the CRUK CTU receiving the first notification of the unexpected reaction
- SUSARs which initially are considered to be non-fatal or non-life threatening but which turn out to be fatal or life-threatening, will be reported as soon as possible and no later than 7 days after the CRUK CTU becoming aware of the reaction being fatal or life-threatening. If this report is incomplete a completed follow-up report will be submitted within an additional 8 days.
- SUSARs which initially are considered to be non-fatal or non-life threatening but which turn out to be fatal or life-threatening, if the initial report has yet to be submitted, will have a combined report submitted

If the assessment of causality provided by the investigator differs from that of the CI (assessment is made on behalf of the sponsor), the opinion of both the investigator and CI will be provided in the SUSAR report.

Investigators will be informed of all SUSARs as they are reported.

The CI will assess if the risk-benefit assessment has been affected by each SUSAR they identify. If the risk-benefit of participation is adversely affected, appropriate prompt action will be decided upon by the CI, Sponsor and Trial Steering Group and implemented by the Trial Management Group.

#### **6.1.7 Other Unexpected Events Requiring Regulatory Reporting**

In addition to SUSARs there may be other events that are relevant in terms of the risk-benefit balance. In addition to SAEs, SARs and SUSARs, all unexpected events that might materially influence the risk-benefit assessment of the IMP or that would lead to changes in the administration of favipiravir or in the overall conduct of a trial will also be reported to the Regulatory Authorities. This includes events which:

- Could be associated with trial procedures which could modify the conduct of the trial
- May be an increase in the rate of occurrence of an expected SAR which may be clinically important

- Potentially could be a significant hazard to the patient population such as a lack of efficacy of the IMP
- Are major safety findings from a newly completed studies (including animal studies)
- Would include the temporary halt of a trial for safety reasons in a trial with the same IMP also conducted by the Sponsor

Other unexpected events must be reported to the required Regulatory Authorities without delay, by the appropriate method (as an urgent safety measure, substantial amendment or early termination of the trial). Regulatory Authorities, Ethics Committees and the Sponsor will be informed of any safety issues that might materially alter the current benefit-risk assessment of the IMP while not falling into the actions for SUSARs noted above.

## **6.2 Pregnancy**

Pregnancy occurring in a clinical trial participant, or the partner of a participant, whilst not considered an AE or a SAE, requires monitoring and follow-up.

Investigators must collect pregnancy information for female trial subjects or female partners of trial subjects. This includes subjects who become pregnant while participating in a clinical trial of an IMP or during a stage where the foetus could have been exposed to the IMP.

### **6.2.1.1 Contraception Requirements**

- Male patients should refrain from fathering a child or donating sperm during the trial and for 3 months after the last administration of favipiravir.
- Patients of childbearing potential and their partners, who are sexually active, must agree to the use of 2 highly effective forms of contraception throughout their participation in the trial and for 3 months after the last administration of favipiravir.

This should be done as part of the consent process by explaining clearly to the patient the potential dangers of becoming pregnant and also providing each patient with information about appropriate medically approved contraception. Two forms of medically approved contraception should be used, such as:

Condom with spermicide, and 1 of the following:

- Oral contraceptive or hormonal therapy (e.g. hormone implants)

- Placement of an intra-uterine device

Acceptable hormonal methods:

- Etonogestrel implants (e.g., Implanon, Norplan) + male condom with spermicide
- Normal and low dose combined oral pills + male condom with spermicide
- Norelgestromin/ethinyl estradiol (EE) transdermal system + male condom with spermicide
- Intravaginal device + male condom with spermicide (e.g., EE and etonogestrel)
- Cerazette (desogestrel) + male condom with spermicide. Cerazette is currently the only highly efficacious progesterone based pill.

In certain restricted circumstances non-hormonal birth control methods are acceptable. These are detailed below:

Acceptable non-hormonal birth control methods include:

- Total sexual abstinence. This must be true abstinence which is in line with the usual preferred lifestyle of the participant (i.e. the participant should not become abstinent just for the purpose of inclusion into the clinical trial).
- Vasectomised sexual partner plus male condom. With participant assurance that partner received post-vasectomy confirmation of azoospermia.
- Tubal occlusion plus male condom with spermicide
- Intrauterine Device plus male condom + spermicide. Provided coils are copper-banded

Contraception should be effective before Day 1 of IMP administration, throughout the trial and for 3 months after completing the trial. It should be explained to male patients that if their partner is pregnant or breast-feeding when the patients enters the trial, the patient should use barrier method of contraception to prevent the unborn baby or the baby being exposed to favipiravir.

#### 6.2.1.2 Pregnancy Reporting Requirements

The Investigator must ensure that all patients are aware at the start of a clinical trial of the importance of reporting all pregnancies (in themselves and their partners) that occur whilst being treated with favipiravir and occurring up to 3 months after the last IMP administration. The Investigator should offer counselling to the patient and/or the partner, and discuss the risks of continuing with the pregnancy and the possible side effects on the foetus. Monitoring of the

patient and the baby should continue until the conclusion of the pregnancy, if the patient or the patient's partner has consented to this.

If a patient or a partner of a patient does become pregnant, the reporting procedures below must be followed:

Any pregnancy occurring in a patient or a patient's partner during treatment with favipiravir) or occurring within 3 months of last administration of favipiravir must be reported to the Pharmacovigilance Office within 24 hours of the site staff becoming aware of it by completing the pregnancy eCRF and following this up, by, immediately faxing or emailing a completed Pregnancy Notification Form (PNF).

It is the Investigator's responsibility to obtain consent from the patient or patient's partner for following-up the pregnancy until outcome. The Pharmacovigilance Department of the CTU will follow-up all pregnancies until the pregnancy outcome via the Investigator, using the PNF.

The Investigator must update the PNF with the outcome of the delivery or if there is a change in the subject's condition such as miscarriage or planned termination. The updated PNF must be faxed or emailed to the PV office as soon as the information becomes available and no later than within 24 hours of first becoming aware of the change in condition.

Any pregnancies which result in a congenital anomaly or birth defect will require to be reported by the Investigator as a SAE. The Pharmacovigilance department will assist with providing guidance on reporting pregnancy outcomes as SAEs. SAEs that are the result of a birth defect will be reported as SUSARs if the CI and Sponsor consider the birth defect to be unexpected.

#### **6.2.2 Medication Errors and Overdose**

Medication errors, while not considered an AE or a SAE, may require monitoring and follow-up. Medication errors that result in SAEs should be reported as SAEs.

An overdose is defined as any dose greater than the highest daily dose included in this document. Any overdose must be recorded. If the overdose is associated with an AE, that AE must be recorded, assessed for seriousness, and reported as an SAE.

Any medication overdoses should be reported to the CRUK CTU Project Manager and Sponsor Pharmacist.

### **6.2.3 Development Safety Update Reports**

Development Safety Update Reports (DSURs) will be prepared for the trial. The reports will be written by the CI and CRUK CTU on behalf of the Sponsor. The CRUK CTU will submit DSURs to the Regulatory Authorities, REC, trial sites, Sponsor and Fuji Film Pharmaceuticals who are supplying the IMP on the anniversary of obtaining the UK Clinical Trial Authorisation.

### **6.2.4 Auxiliary Medicinal Products (AMPs)**

There are no AMPs in this protocol.

### **6.2.5 Reference Safety Information**

The section of the IB titled Reference Safety Information (RSI) supplied by Fuji Film Pharmaceuticals for favipiravir will act as the RSI for the trial. Fuji Film Pharmaceuticals is responsible for supplying the Sponsor with updated IBs within 14 days of UK regulatory approval. However, only the RSI section of the IB with current regulatory approval to act as the RSI for the GETAFIX trial, will be used to assess expectedness (with the proviso that the RSI must remain consistent for each DSUR reporting period). Investigators will be supplied with IBs and updated IBs when the Sponsor and CI conclude the update will assist with the clinical management of trial patients.

### **6.2.6 Changes to the RSI or Risk-Benefit Assessment**

If changes to the RSI include the addition of new reactions now considered expected, an update that impacts on patient safety or if the risk-benefit assessment or clinical management of trial participants is affected by an update to the RSI, then the RSI will not change for the duration of the DSUR reporting period however the updated IB will:

- Circulated to trial sites
- A front sheet document for use when the risk benefit or clinical management has changed, will accompany the reference IB and provide guidance on the current RSI and IB be referred to for the clinical management of trial patients

- If patient safety/or the risk-benefit assessment has changed and/or new expected reactions have been added, then approval to use the updated IB as the RSI, will be made by submitting a substantial amendment to the Regulatory Authority.
- If new reactions are added to the IB as “expected”, implementing the updated IB for assessing SARs will not occur until regulatory approval is received for the updated IB and once the new DSUR reporting period starts

Changes that impact on patient safety or alter the risk-benefit assessment may require changes to the trial documentation such as the patient information sheet. The CI on behalf of the sponsor will identify any such required changes. The CTU will seek approval of the changes, as required by the clinical trial regulations.

### 6.2.7 Requirements for DSUR Reporting and the Maintenance of RSI in the Follow-Up Period

DSURs will continue to be submitted and the RSI maintained until the last patient has attended for their last follow-up visit.

## 7 STATISTICS AND DATA ANALYSIS

### 7.1 Trial Design and Sample Size

The study is designed as an open-label randomised (1:1) phase II/III study which allows for early stopping for lack of efficacy or clear superiority in the experimental arm.

The study is powered to detect an improvement corresponding to an odds ratio of 1.95 in the cumulative odds of the WHO COVID 10-point ordinal severity scale assessed at day 15. This is equivalent to the probability of a patient having a better outcome at this time if allocated to experimental as compared to control of 66% (50% under null hypothesis). The following table illustrates that improvement:-

|                              | WHO COVID 10-point ordinal severity scale                                                                                | Assumed percentages on control arm at day 15* | Percentages on experimental arm at day 15 with odds ratio=1.95 |
|------------------------------|--------------------------------------------------------------------------------------------------------------------------|-----------------------------------------------|----------------------------------------------------------------|
| Death                        | Death                                                                                                                    | 11%                                           | 6.0%                                                           |
| Hospitalized; severe disease | Mechanical ventilation pO 2 /FIO 2 <150 and vasopressors, dialysis or ECMO                         | 5%                                            | 2.9%                                                           |
|                              | Mechanical ventilation pO 2 /FIO 2 >150 ( SpO 2 /FIO 2 >200) or vasopressors | 7%                                            | 4.4%                                                           |

|                            |  |                                                                                      |     |       |
|----------------------------|--|--------------------------------------------------------------------------------------|-----|-------|
|                            |  | ICU - intubation & mechanical ventilation, $pO_2/FIO_2 > 150$ or $SpO_2/FIO_2 > 200$ | 5%  | 3.3%  |
| Hospitalized; Mild disease |  | Hospitalized oxygen by NIV or High flow                                              | 13% | 9.6%  |
|                            |  | Hospitalized on supplemental oxygen                                                  | 13% | 11.3% |
|                            |  | Hospitalized not on supplemental oxygen                                              | 12% | 12.3% |
| Ambulatory                 |  | Symptomatic – assistance needed                                                      | 2%  | 2.3%  |
|                            |  | Symptomatic – independent                                                            | 16% | 21.8% |
|                            |  | Asymptomatic – viral DNA detected                                                    | 16% | 27.0% |

\*Abstracted from figure 6 in ISARIC COVID-19 Report: 02 April 2020

To detect this magnitude of difference with 90% power at the 5% 2-sided level of statistical significance requires 302 patients (151 per arm). This allows for the possibility of early stopping at two interim analyses after primary outcome data is available for 128 and 202 patients. The interim analyses are detailed in 7.3.

### 7.1.1 Analysis Plan

Analyses to account for any non-trial treatment for COVID-19 will be investigated prior to any analyses being undertaken. The decision regarding whether adjustments are required may be based on a blinded assessment of the number of patients who receive non-trial treatment for COVID19 prior to each outcome time-point being reached. Analyses will be used to remove confounding from non-trial COVID19 treatment, and may include inverse probability weighting.

### 7.1.2 Primary Efficacy Analysis

The primary analysis will use cumulative odds ordinal regression with proportional odds. The model terms will be study arm and the minimisation factors used for randomisation. The odds of a patient having a better outcome if allocated to the experimental arm will be estimated along with the associated 95% confidence interval. A Forest plot illustrating treatment effect odds ratios by minimisation factor categories will also be provided. . A test for interaction will be conducted to assess whether the effect of treatment arm depends on the other clinical factors used in the minimisation algorithm.

It will not be possible to distinguish between 0 and 1 on the WHO COVID 10-point ordinal severity scale so these will be combined in analyses.

### **7.1.3 Secondary Efficacy Analysis**

Proportion of patients meeting level 7 or above on the WHO COVID 10 point ordinal severity scale or dead by day 29; Overall survival over the 60 days; Viral clearance on or before d8 of treatment (inpatients)

These end-points will be tabulated and examined using logistic regression incorporating terms for study arm and the minimisation factors used for randomisation.

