| Pregnancy Test                                                      | X                              |                 |          |                 |          |          |          |          |                 |          |           |                        |                                    |                                     |
| PK testing                                                          |                                | X               |          | X               |          | X        |          |          | X               |          | X         |                        |                                    |                                     |
| COVID19 Health
and Wellbeing
Follow up
Survey
(Appendix 3)          |                                |                 |          |                 |          |          |          |          |                 |          |           | X                      | X                                  | X                                   |

1. Observations: Heart rate, temperature, oxygen saturations, blood pressure, respiratory rate
2. IMP should start to be administered within 24 hours of randomisation
3. Bloods/Nasopharyngeal swabs can be taken +/- 48 hours from scheduled time point unless otherwise specified. Screening bloods/NP swabs should be performed within 96 hours of randomisation
4. Nasopharyngeal swabs on day 1 should be taken as close to T0 (time of first drug administration) as possible
5. Patients discharged prior to day 15 should follow the outpatient schedule of assessments from point of discharge. Patients should return for clinic visit where possible, or be followed up by phone call if unable to attend

6. Follow-up visit at day 29 and 60 may be performed by telephone if patient is unable to attend clinic
7. Serum pregnancy test, for patients of child bearing potential only
8. Screening COVID-19 test can be done using any valid method of testing
9. PK Samples should be taken at the following times:

- Day 1: pre dose and 0.5 hours post dose
- Day 3: pre and 0.5 hours post dose
- Day 5: pre and 0.5 hours post dose
- Day 8: Pre dose
- Day 10: Pre dose

In addition, 16 volunteers (8 male, 8 female) will have more frequent sampling for PK on days 1 and 3 after either dose that day. Hours post dose: 0.5, 1, 2, 7, 12

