### **Day 1-10^1**

WHO COVID 10 point ordinal severity scale assessment (daily – worst value in last 24 hours)

Documentation of concomitant medications (daily)

Assessment of adverse events (daily)

Routine observations/vital signs\* (daily)

Routine clinical blood tests: days 1,3,8,11 (+/- 48 hours)

Blood tests for immunological and epigenetic testing: days 1, 3 (+/- 48 hours)

Symptom directed clinical examination if clinically indicated

Administration of IMP (if applicable)

Nasopharyngeal swab (for SARS-CoV-2 PCR assessment and Viral Load): days 1 (at time of first dose), 3, 8, 10, 13 (+/- 48 hours)

Pharmacokinetic samples: according to the sample schedule (Appendix 5)

 Patients discharged during this time should follow the outpatient trial schedule. The timing of the first dose of favipiravir should be documented as Time zero (T0). The nasopharyngeal swab should be taken as close to this time as possible.

 On day 8, two swabs should be taken – one to be sent for immediate COVID-19 testing by any valid method, the other to be stored for later analysis of viral load.

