#### Change in viral load

Viral load will be summarised and compared between treatment groups using an area under curve (AUC) approach standardised for the period on study and using the baseline value as a covariate.

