#### Viral clearance on or before d8 of treatment (outpatients)

This will be tabulated and examined using logistic regression incorporating terms for study arm and the minimisation factors used for randomisation, if the number of patients is sufficient.

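### The inpatient day-8 viral-clearance model gives up a little power by not adjusting for baseline viral load, which the trial already collects

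*Protocol*

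**What the plan says.** Protocol section 7.1.3 groups inpatient viral clearance on or before day 8 with two other secondary endpoints and gives one model for all three: "These end-points will be tabulated and examined using logistic regression incorporating terms for study arm and the minimisation factors used for randomisation". Section 7.1.4 gives the exploratory outpatient clearance endpoint the same terms, conditionally: "logistic regression incorporating terms for study arm and the minimisation factors used for randomisation, if the number of patients is sufficient".

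Section 3.4 lists the minimisation factors: site, age band, hypertension or obesity, symptom duration under 7 days (yes, no, unknown), sex, and baseline WHO score (2 or 3 against 4). Viral load is not among them.

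Baseline viral load is scheduled. For inpatients, section 4.2.1 (Day 1-10) has "Nasopharyngeal swab (for SARS-CoV-2 PCR assessment and Viral Load): days 1 (at time of first dose), 3", and note 4 to the inpatient schedule says "Nasopharyngeal swabs on day 1 should be taken as close to T0 (time of first drug administration) as possible". For outpatients, the schedule table marks a viral-load swab at screening.

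For change in viral load, section 7.1.4 plans an AUC comparison "standardised for the period on study and using the baseline value as a covariate". Clearance itself is defined under the objectives table as a negative PCR.

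**The concern.** How much virus a patient carries at the start plausibly predicts whether the PCR is negative a week later. A logistic model that leaves out a prognostic covariate estimates an odds ratio pulled towards 1 and has less power than a model that includes it. The protocol names the model terms, so this is a stated choice and not merely something unsaid.

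The minimisation factors offer little in its place. Entry is limited to WHO scores 2, 3 and 4, and 4 is the only hospitalised level among them (Appendix 1). If the inpatient group is defined by status at baseline, the WHO-score factor is constant within it and adjusts for nothing. The nearest remaining stand-in is the two-way symptom-duration flag with its unknown level.

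At stake is the precision of one secondary endpoint. It is close to the drug's rationale, since the Background section argues from shorter time to viral clearance. It is also measured only in the inpatient part of 302 patients, where power is scarcest.

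**Working it through.** **The plan's own figure.** None exists for viral clearance. The only sample size is 302 for the primary ordinal endpoint, and it reproduces. The Whitehead formula is n per arm = 6(z_a + z_b)² / {ln(OR)² [1 − Σp̄³]}, with OR 1.95 and the control distribution in section 7.1. It gives 6 × 10.51 / (0.446 × 0.978) ≈ 144.6 per arm, or 289.1 in total for a fixed design. With the boundaries in section 7.2, 302 patients give 90.1% power. This says nothing about clearance, so the size of the present point rests on assumed inputs.

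**Assumed inputs (not in the documents).** Inpatient number, clearance rates per arm, and the association between baseline log viral load and clearance.

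**Check 1: latent-normal model, 3,000 trials per cell.** Clearance depends on a latent normal variable with correlation ρ to standardised baseline log viral load. Logistic regression is fitted on arm alone and on arm plus baseline, with significance at |z| > 1.96.

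| Clearance | N | ρ | Power without | Power with | Gain (points) |
|---|---|---|---|---|---|
| 30% v 50% | 160 | 0.3 | 0.739 | 0.765 | 2.6 |
| 30% v 50% | 160 | 0.5 | 0.726 | 0.806 | 8.0 |
| 30% v 50% | 160 | 0.7 | 0.726 | 0.883 | 15.7 |
| 30% v 50% | 120 | 0.5 | 0.612 | 0.675 | 6.3 |
| 30% v 50% | 80 | 0.5 | 0.461 | 0.507 | 4.6 |
| 40% v 60% | 160 | 0.5 | 0.706 | 0.784 | 7.8 |
| 40% v 60% | 120 | 0.5 | 0.623 | 0.676 | 5.3 |

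Repeat runs agree to within 1 to 2 points and put the gain at ρ = 0.3 between 0 and 3 points for 80 to 160 inpatients. The simulation standard error of each power is at most √(0.25/3000) ≈ 0.9 points.

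To read ρ as an odds ratio per SD, take exp(1.7 × ρ/√(1−ρ²)):
- ρ = 0.3: exp(1.7 × 0.314) ≈ 1.7
- ρ = 0.5: exp(1.7 × 0.577) ≈ 2.7
- ρ = 0.7: exp(1.7 × 0.980) ≈ 5.3

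**Check 2: logistic model, 40% v 60%, 1,500 runs per cell.** Power without → with baseline viral load, by odds ratio per SD. The standard error of each power is at most √(0.25/1500) ≈ 1.3 points.

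| N | 1.0 | 1.5 | 2.0 | 3.0 |
|---|---|---|---|---|
| 100 | 0.551→0.533 | 0.545→0.540 | 0.549→0.557 | 0.553→0.611 |
| 150 | 0.677→0.691 | 0.669→0.707 | 0.683→0.741 | 0.668→0.776 |
| 200 | 0.846→0.837 | 0.835→0.829 | 0.808→0.830 | 0.808→0.864 |
| 302 | 0.937→0.941 | 0.929→0.945 | 0.932→0.957 | 0.929→0.973 |

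A weak covariate gains nothing beyond simulation error. At an odds ratio of 3, a little above ρ = 0.5, the gain is about 4 to 11 points.

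**Type I error.** Without the covariate it was 0.042 to 0.061 across all cells of check 2, so it stays near 5%.

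**Chance imbalance.** The difference in mean baseline between two equal arms has SD 2/√N in units of the covariate SD, so P(|difference| > 0.3 SD) = 2[1 − Φ(0.15√N)]. That is 13% at N = 100, 7% at 150, 3% at 200 and 1% at 302. Within such trials, at odds ratios of 2 to 3 and N = 100 to 200, false positives were about 8% to 18% without the covariate and 3% to 7% with it. These rates rest on few runs: at N = 200, about 0.034 × 1,500 = 51 per cell.

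**Limit.** In both checks the model without viral load holds arm alone, whereas the planned model also holds the minimisation factors. The assumed association must therefore be read as what remains after those factors.

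**The case against.** The strongest reply is that nothing here is an error. Logistic regression on arm and minimisation factors is a valid, prespecified analysis, and further covariates are often settled in an SAP, which is not shown. The first half stands in full. The second stands in part: the protocol names the terms of this model, so viral load is outside it as written, but adding it is an improvement and not the repair of a fault.

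A reader might infer that the planned test lets a chance imbalance pass as a drug effect. It does not in the sense of error control: averaged over randomisations, such imbalances are already inside the 5%. The higher conditional rates describe the minority of badly imbalanced trials.

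A reader might also infer that the protocol contradicts itself, since the AUC analysis adjusts for its own baseline and the clearance analysis does not. The two are not parallel. Clearance is a negative PCR, and every patient is test-positive at entry. Viral load is a related but different measure: the inpatient day-8 clearance test is done at once by any valid method in an NHS laboratory, while viral load comes from a second, stored swab analysed in an academic laboratory (schedule note 11; sections 4.3.2 and 4.3.3). The AUC analysis also means that one baseline-adjusted virological comparison is already planned.

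The practical objections to the covariate stand too. The day-1 swab is only to be near the first dose, so it may follow it, and controls have no first dose. For outpatients, the schedule table shows a screening viral-load swab but the section 4.2.2 screening list does not. The day-8 outpatient swab is optional, and that model is run only if numbers suffice.

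**Conclusion.** The point holds as a minor matter of efficiency, mainly for the inpatient secondary endpoint. The planned test is valid. Leaving out baseline viral load costs about 0 to 8 power points for a weak to moderately strong residual association (ρ 0.3 to 0.5, 80 to 160 inpatients). The cost is larger only if the association is very strong, for example about 16 points at ρ = 0.7 with 160 inpatients. The upper end of 5 to 8 points should not be read as the expected loss: it needs an odds ratio near 2.7 per SD after the minimisation factors, for which the documents give no support. Inpatient number, clearance rates and correlation are all assumed. The primary endpoint, the interim boundaries and overall error control are unaffected.

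**What to change.** In section 7.1.3, add log10 baseline viral load as a continuous covariate in the inpatient viral-clearance logistic model.

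- Use only swabs taken before the first dose; for controls, use a prespecified window around randomisation. Taking simply the nearest swab could adjust for a post-dose value in one arm only.
- Use mean imputation or a missing-indicator for absent baselines, so that no randomised patient is dropped.
- Use the same definition of baseline in the viral-load AUC analysis, which needs one anyway.
- In section 7.1.4, apply the term to the outpatient model only if that model is run and enough screening viral-load swabs exist.
- Because the trial is open-label, fix this before any outcome data are examined.

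The cost is one covariate and a short baseline definition, with no new inpatient samples. The small downside is that the odds ratio becomes conditional on viral load and some baselines will be imputed.
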